### SUMMARY

**Rationale:** Clinical guidelines recommend routine follow up (RFU) with X-ray and clinical visit at 1 year after Total Hip Arthroplasty (THA) and Total Knee Arthroplasty (TKA). However, evidence for (cost-)effectiveness of RFU is lacking. Registry data show excellent survival of THA and TKA and the added value of RFU can be questioned, as revisions are rare and seldom without symptoms. However, replacing RFU with a final follow up within 3 months and thereafter only check-ups on demand (COD), could lead to risks such as missed complications, lower patient satisfaction, or decreased physical function.

**Objective:** To investigate the (cost-)effectiveness of COD compared to RFU at 1 year, up to 2 years after THA and TKA.

**Study design:** A hybrid effectiveness (de-)implementation trial type II, with a stepped-wedge cluster trial design.

**Study population:** Patients scheduled for THA or TKA who experience pain and disability in the knee or hip joint due to osteoarthritis, and aged  $\geq 50$  years at the time of the surgery.

**Intervention:** Check-up on demand (COD) by the patient or healthcare provider (HCP), after a final clinical visit with X-ray within 3 months to diagnose complications and provide instructions when to contact an HCP.

**Comparator:** Routine follow up (RFU) consisting of an X-ray and clinical visit within 3 months and at 1 year after surgery. Patients are welcome to contact an HCP in case of pain, concerns or other symptoms associated with their prosthesis at any time.

**Main study parameters/endpoints:** The main study parameters are clinical and process outcomes. The clinical outcome is patient-reported physical function, measured with the PROMIS questionnaire, 2 years after surgery (1 year after RFU or COD). The process outcome is healthcare consumption, including X-rays and clinical visits.

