## 2. OBJECTIVES

**Primary Objective:** At 2 years after surgery, what is the effect of a final follow up within 3 months combined with check-ups on demand (COD) compared to routine follow-up (RFU) within 3 months and at 1 year after total hip and knee arthroplasty (THA and TKA) on physical function (effectiveness) and clinical visits (implementation)?

**Secondary Objective(s):** At 2 years after surgery, what is the effect of a final follow up within 3 months combined with COD compared to RFU within 3 months and at 1 year after THA and TKA on complications, surgical interventions, quality of life (QoL), pain and costs.

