### **10.1 Primary study parameter(s)**

PROMIS physical function will be presented as mean with standard deviation, assuming normality. Differences in PROMIS physical function between the RFU and COD groups will be compared using linear mixed models, with repeated measurements clustered within participants and participants clustered within hospitals (random intercepts). The intervention group (RFU vs. COD), baseline PROMIS physical function, and time points (12, 15, 18 and 24) will be included as fixed effects to determine the crude effect of the intervention at each time point, with the primary outcome at 24 months. Given the stepped wedge design, the duration of the intervention period differs between sites. Therefore “period” is also included as a fixed effect. To assess of the effect of COD might increase over a longer period of time, an interaction term (period \* intervention) will be tested for these possible time effects for the primary outcome.

For healthcare consumption, the percentage of patients who have had at least one clinical visit or X-ray 1 year after RFU or COD will be presented for each group. Additionally, the average number of visits and X-rays per patient will be reported.

A logistic generalized linear mixed model (GLMM) will be used to compare the presence or absence of visits/X-rays (yes/no per patient) between RFU and COD. A Poisson regression analysis will be performed to assess the average number of visits and X-rays per patient, adjusting for potential confounders. Interaction terms between the confounders and the intervention group will also be included to explore whether certain patient characteristics influence the differences in healthcare consumption between RFU and COD.

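### The PROMIS model in Section 10.1 has no intervention-by-time-point term, so its listed terms cannot give the 24-month effect they are meant to estimate

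*Protocol*

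**What the plan says.** The target is fixed at 24 months. The primary objective (Section 2) opens with "At 2 years after surgery, what is the effect of a final follow up within 3 months combined with check-ups on demand (COD", and the Summary describes physical function as "measured with the PROMIS questionnaire, 2 years after surgery (1 year after RFU or COD".

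Section 10.1 specifies a linear mixed model with "repeated measurements clustered within participants and participants clustered within hospitals (random intercepts". Intervention group, baseline PROMIS and the four time points (12, 15, 18 and 24 months) are to be "included as fixed effects to determine the crude effect of the intervention at each time point, with the primary outcome at 24 months". Period is then added as a further fixed effect, for this reason: "Given the stepped wedge design, the duration of the intervention period differs between sites". The one interaction named for PROMIS is period by intervention, which "will be tested for these possible time effects for the primary outcome".

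Section 4.4 frames PROMIS as a non-inferiority comparison: margin 3, SD 9, 190 patients per group for 90% power with a one-sided 97.5% interval, raised to 250 for loss to follow-up, for each joint.

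**The concern.** A model with intervention and time point as main effects has a single intervention coefficient that applies to all four visits. It cannot give an effect at each visit, nor one at 24 months. The period-by-intervention term does not supply this, because period is introduced through the stepped-wedge schedule and listed separately from the time points. It describes where a site stands in the roll-out, not months since a patient's surgery.

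The direction of the error matters. The protocol describes 24 months as one year after RFU or COD, yet the 12-month score enters the model as an outcome of equal standing. The harm that the trial must exclude is loss of function from problems missed once the 1-year check is dropped, and this could plausibly emerge after 12 months. Averaging in earlier visits would then shrink the estimated deficit, which in a non-inferiority trial helps the claim.

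**Working it through.** **1. The plan's own figure.** Inputs from Section 4.4: margin 3, SD 9, true difference 0, one-sided alpha 0.025, power 90%. n per group = 2 × 9² × (1.960 + 1.282)² / 3² = 189.2, so 190, as stated. Allowing for 20-25% loss gives 238 to 254, which brackets the planned 250. This is a single-time-point calculation, so it matches a 24-month contrast and the present point does not change it.

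**2. What the listed terms estimate.** With complete data and random intercepts, every patient contributes the same four visits. The intervention coefficient is then the difference in patient means:

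estimate = (δ12 + δ15 + δ18 + δ24) / 4

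This equals δ24 under a constant effect, but not in general. With dropout the weights move somewhat towards the earlier visits.

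**3. Assumed effect paths.** The protocol gives none. Each path below has a true 24-month deficit of 3.

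| Deficit at 12/15/18/24 months | Estimate from listed terms |
|---|---|
| 3, 3, 3, 3 (constant) | 3.00 |
| 0, 3, 3, 3 (step after 12 months) | 2.25 |
| 0, 0.75, 1.5, 3 (linear) | 1.31 |
| 0, 0, 0, 3 (late) | 0.75 |

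A small mixed-model simulation of the linear path with about 22% dropout gave mean estimates of -1.34 from main effects only and -3.05 at 24 months with the interaction (12 runs, a check only).

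**4. Chance of claiming non-inferiority, ignoring clustering and period.** Take 190 per group, SD 9 and an assumed within-patient correlation ρ of 0.6 to 0.8.

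SE of the average = 9 × √(2/190) × √((1 + 3ρ)/4) = 0.923 × 0.837 = 0.77 at ρ = 0.6, and 0.923 × 0.922 = 0.85 at ρ = 0.8.

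P(claim) = Φ((3 − averaged deficit)/SE − 1.96)

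Linear path: Φ(1.6875/0.773 − 1.96) = Φ(0.22) = 59% and Φ(1.6875/0.851 − 1.96) = Φ(0.02) = 51%. A valid 24-month contrast gives Φ(−1.96) = 2.5%.

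**5. The same with the plan's period term.** Inputs: Table 1 recruitment halved per joint (250 per arm), 76% retained (190 per arm), SD 9, ρ 0.6 to 0.8, assumed hospital ICC 0 to 0.05, and period taken as blocks of 1, 2 or 3 calendar months. The protocol states neither the ICC nor the period width. In Table 1 the two arms recruit in the same month only in January and February 2026, so period adjustment removes much of the information. Generalised least squares on the hospital-by-month means gives an SE of the averaged coefficient of about 1.93 to 2.70.

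Linear path: Φ(1.6875/2.70 − 1.96) = Φ(−1.34) = 9%, up to Φ(1.6875/1.93 − 1.96) = Φ(−1.09) = 14%.

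**6. All paths by the same formula.**

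| Path | No clustering or period (SE 0.77-0.85) | With period term (SE 1.93-2.70) |
|---|---|---|
| Constant | 2.5% | 2.5% |
| Step after 12 months | 14-16% | 5-6% |
| Linear | 51-59% | 9-14% |
| Late | 75-83% | 13-21% |

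For a linear path reaching a deficit of 4, the averaged deficit is (0 + 1 + 2 + 4)/4 = 1.75. The chance is 31-37% without the period term and 7-10% with it.

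Baseline adjustment is left out throughout, because the plan gives no correlation between baseline and follow-up scores.

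**The case against.** The strongest reply is that this is an omission in wording. The sentence that lists the terms also says that an effect at each time point is wanted and that 24 months is primary, which implies an interaction. A statistical analysis plan, mentioned in Section 12.1 but not available here, may spell it out. This stands as to intent. A reader might infer that the sponsor means to report an average over 12 to 24 months, and the text does not support that. But the protocol does more than leave a detail open: it lists the terms, names a different interaction and states a purpose that those terms cannot serve. Choosing between the average and the 24-month contrast after data are seen would be a post hoc choice of the primary result.

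A second reply concerns size, and it is largely right. A reader might take 51-59% as the trial's false-claim rate. That figure treats the trial as a simple comparison of 190 with 190 and ignores the plan's own period term. With that term the same path gives 9-14%, still above 2.5% but far smaller. All these figures rest on an assumed path. A constant effect gives no bias, and with a deficit that fades after 12 months the averaging would count against COD.

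Third, the arms cannot be assumed identical at 12 months. COD instructions are given at the visit within 3 months, and the 30-day window under Table 2 governs questionnaire timing. Nothing ties the 12-month questionnaire to the date of the 1-year visit. The zero at 12 months is therefore an assumption of the illustration.

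**Conclusion.** The point holds as a defect of the written specification: the fixed effects in Section 10.1 cannot produce the 24-month effect that the objective, the Summary and the same section call primary. That conclusion needs no assumption about the data.

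The consequence is conditional. If a deficit grows after 12 months, the averaged coefficient understates it and favours non-inferiority. Under the assumed linear path a 3-point deficit appears as about 1.3, and the chance of a claim is about 9-14% with the period term (51-59% without it), against at most 2.5% nominally. These ranges depend on the assumed path, within-patient correlation, ICC and period width. The documents do not support a single figure, nor a statement that the trial will be biased. Because the term decides the primary estimate and is cheap to add, it should be corrected before analysis.

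**What to change.** In Section 10.1, add intervention by time point (12, 15, 18 and 24 months, categorical) to the PROMIS model. Name the 24-month COD-minus-RFU contrast, with its confidence interval set against the margin, as the single primary estimate, and report 12, 15 and 18 months as secondary. A particular covariance structure, such as unstructured, is not needed to cure the contradiction.

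In Section 10.2, add the same interaction for EQ-5D-5L at its modelled time points (15, 18 and 24 months), since the secondary objectives are also set at 2 years. For NPRS, first reconcile the modelled 15 and 18 months with Table 2, which schedules NPRS only before surgery, at 1 year and at 24 months. An interaction at visits without data cannot be fitted.

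The cost is one sentence per model and a somewhat wider interval than for the average. In the simple comparison the SE is 0.92 for the 24-month contrast against 0.77-0.85 for the average. No change to data collection or to the stated 190 per group follows from this point.

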## **5. TREATMENT OF RESEARCH PARTICIPANTS**

Routine Follow Up (RFU): X-ray and clinical visit following THA and TKA guidelines within

standard care: within 3 months and at 1 year after surgery. Patients are welcome to contact a HCP (i.e. general practitioner, physical therapist or hospital) in case of pain, concerns or other symptoms associated with their prosthesis at any time. RFU after THA and TKA is part of the guidelines “Totale heupprothese” and “Totale knieprothese” (5,6).

Check-Up on Demand (COD): final clinical visit with X-ray within 3 months and instructions how and when to contact a HCP. Further check-ups are scheduled only on demand (COD) by the patient or HCP. Patients are welcome to contact a HCP (i.e. general practitioner, physical therapist or hospital) in case of pain, concerns or other symptoms at any time (similar to current standard care).

In clinical practice, there is already variability in how follow-up after total hip or knee arthroplasty is conducted. Both RFU and variations of COD are utilized across different hospitals, with the choice of approach sometimes varying between individual orthopedic surgeons. The Dutch Orthopaedic Association (NOV) has confirmed that the interventions evaluated in this study are considered part of standard care.

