## **8. METHODS**

### **8.1 Study parameters/endpoints**

#### **8.1.1**

##### **Main study parameter/endpoint**

- Clinical: PROMIS physical function
- Process (healthcare consumption): number of clinical visits and X-rays

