### 8.1.3

#### **Other study parameters**

- Patient characteristics (e.g. age, gender, BMI, ASA score, ethnicity, employment status, and education level).
- Surgical characteristics (e.g. surgical approach, prosthesis type and fixation method, surgical duration, and intra-operative complications)
- Postoperative characteristics (e.g. length of hospital stay, in-hospital complications and discharge destination)
- Healthcare consumption, complications, and surgical interventions from the time of THA/TKA up to one year postoperatively

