## **8.3 Study procedures**

Patients scheduled for total THA or TKA will be invited to participate in the study prior to their surgery. This timing ensures that participation is not influenced by the surgery itself, and a patient's potential preference for follow-up care.

Information on patient background will be collected to explore potential differences in follow-up needs, including among patients with different ethnic backgrounds. Previous research shows that people with a migrant background visit specialists and hospitals less often than

native Dutch patients with similar health and SES (19). Acknowledging the sensitivity of this topic, a 'prefer not to say' option is provided.

If the center where the patient undergoes surgery is in RFU phase, follow-up visits will be scheduled within 3 months and 1 year postoperatively. If the center is in the COD phase, patients will receive instructions during their 3-month follow-up on when and how to contact a HCP in case of concerns or complaints. In the COD phase, no standard 1-year follow-up visit will be scheduled.

Participants will be followed up to 2 years after surgery, i.e. 1 year after RFU or COD. The primary outcome, costs and the EQ-5D-5L will be measured pre-operative, at 1 year after surgery and at 15, 18 and 24 months after surgery. The other outcomes will be measured pre-operative (baseline) and at 1 year and 2 years after surgery (endpoint). Figure 1 depicts a flowchart of study participation.

[figure not shown]

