### **10.3 Cost-effectiveness**

The trial-based economic evaluations will focus on the primary outcome (PROMIS physical function) and QALYs, following the intention-to-treat principle. Two perspectives will be considered: 1) healthcare and 2) societal. QALYs will be calculated by multiplying utility values (based on EQ-5D-5L and valued using the Dutch tariff) by health state durations (22,23). Resource utilization will be assessed via cost questionnaires (15, 18 and 24 months after surgery) and valued according to the “Dutch manual of costing” (24). Missing data will be handled with multivariate imputation by chained equations (25). Societal costs include healthcare, absenteeism, presenteeism, unpaid productivity, and informal care; healthcare costs cover only the formal Dutch healthcare sector. Linear mixed models will estimate cost and effect differences, accounting for clustering (e.g., hospital level). Incremental cost-effectiveness ratios (ICERs) will be calculated as cost differences divided by effect differences, with uncertainty assessed through non-parametric bootstrapping nested within multiple imputation. Results will be visualized in cost-effectiveness planes and acceptability curves (26,27). Sensitivity analyses, including complete-case analysis, will test result robustness (23). The budget impact analysis (BIA) will use ZonMw’s BIA tool, based on Dutch incidence data. Perspectives include societal, government (Budget Kader Zorg), and insurer. Scenarios include: 1) RFU-only implementation, 2) COD for all patients, and 3) COD for specific subgroups (e.g., low-complication risk), defined by study results. Costs will be valued using Dutch standard costs, tariffs set by the Dutch Healthcare Authority (NZA), or average insurer tariffs. The cost-effectiveness and BIA analyses will adhere to the 'Dutch guideline for economic evaluations in health care' (28).

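### The process primary endpoint is read from month 12 although the strategies part after the visit within 3 months, and no rule says whether the scheduled 1-year RFU visit and X-ray count

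*Protocol*

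**What the plan says.** Section 8.1.1 defines the process endpoint without a time window: "Process (healthcare consumption): number of clinical visits and X-rays". The primary objective (section 2) compares the two follow-up strategies at 2 years after surgery on physical function and clinical visits.

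A window appears only in section 10.1, where "the percentage of patients who have had at least one clinical visit or X-ray 1 year after RFU or COD will be presented". The same section plans a mean number of visits and X-rays per patient, a logistic mixed model for any versus none, and a Poisson model for the number. It repeats no window for these and does not mention the scheduled 1-year visit.

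The phrase is explained elsewhere. Section 8.3: "Participants will be followed up to 2 years after surgery, i.e. 1 year after RFU or COD". The Summary, for the clinical outcome: "2 years after surgery (1 year after RFU or COD". The 12-month column of Table 2 is labelled as the RFU or COD time point.

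Earlier use is listed under other study parameters in section 8.1.3: "Healthcare consumption, complications, and surgical interventions from the time of THA/TKA up to one year postoperatively". Section 10.4 gives the other parameters it names a descriptive and confounder-adjusting role.

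On when the strategies diverge, section 5 says of COD, after the final visit within 3 months: "Further check-ups are scheduled only on demand (COD) by the patient or HCP". Under RFU a visit and X-ray are scheduled at 1 year (8.3, Table 2); under COD they are not.

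On costs, section 8.3 says: "The primary outcome, costs and the EQ-5D-5L will be measured pre-operative, at 1 year after surgery and at 15, 18 and 24 months after surgery". Section 10.3 says: "Resource utilization will be assessed via cost questionnaires (15, 18 and 24 months after surgery". Table 2 agrees with 10.3.

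**The concern.** The implementation question is how many visits and X-rays the COD strategy saves, net of those that patients or providers ask for instead. Nothing happens to a COD patient at month 12. Their follow-up changed at the visit within 3 months, so any substitute for the routine visit can occur from then on. A window opening at month 12 leaves out the first nine months or so in which that can happen.

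The one visit that the trial removes also sits on the opening boundary of the window, with no rule on whether it counts. The percentage, the yes/no test and the count each mean something different under the two readings. This is a main endpoint of the trial, so the choice should not be open once data have been seen.

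**Working it through.** **The plan's own figure.** The only computed sample size is for PROMIS (section 4.4): n = 2(1.960 + 1.282)² × 9² / 3² = 2 × 10.51 × 9 = 189.1, hence 190 per group, as stated. With 24% loss, 190/0.76 = 250. There is no corresponding calculation for the process endpoint. The protocol gives no visit rates or attendance figure, so every rate below is an assumption.

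**Step 1: the window.** The Summary and 8.3 equate 2 years after surgery with 1 year after RFU or COD, so the reference point is month 12 and the end is month 24. Section 8.1.3 puts use up to 12 months outside the primary and secondary endpoints. Together these give months 12 to 24.

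**Step 2: net visits saved per patient (RFU minus COD).** Let s be attendance at the scheduled 1-year visit, a_R and a_C the mean unscheduled visits in months 3–12, and b_R and b_C those in months 12–24.

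- Months 3–24, scheduled visit counted: s + (a_R − a_C) + (b_R − b_C)
- Months 12–24, scheduled visit counted: s + (b_R − b_C)
- Months 12–24, scheduled visit not counted: b_R − b_C

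The second exceeds the first by a_C − a_R, whatever the other rates are. The third differs from the second by s.

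Illustration with s = 0.95:

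| a_R | a_C | b_R | b_C | 12–24, counted | 12–24, not counted | 3–24, counted |
|---|---|---|---|---|---|---|
| 0.2 | 0.2 | 0.2 | 0.2 | 0.95 | 0.00 | 0.95 |
| 0.2 | 0.4 | 0.2 | 0.2 | 0.95 | 0.00 | 0.75 |
| 0.2 | 0.6 | 0.2 | 0.3 | 0.85 | −0.10 | 0.45 |
| 0.2 | 0.2 | 0.2 | 0.4 | 0.75 | −0.20 | 0.75 |
| 0.2 | 0.8 | 0.2 | 0.5 | 0.65 | −0.30 | 0.05 |

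Rows 1 and 4 show no distortion from the window when months 3–12 are equal in both groups. Row 5 is an extreme case.

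**Step 3: the yes/no test.** Two-sided 5%, 190 per group, no clustering, normal approximation: power = Φ{[|p₁ − p₂| − 1.96√(2p̄(1 − p̄)/n)] / √[(p₁(1 − p₁) + p₂(1 − p₂))/n]}.

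- *Scheduled visit counted.* RFU 85–99% against COD 10–50%: power is about 1.00 throughout, and 5 to 36 patients per group would give 90%. The schedule largely settles the result.
- *Scheduled visit not counted.* With equal on-demand proportions the expected difference is zero, although each attending RFU patient made one extra visit. A COD excess of 5 points over 10%, 20% or 30% has power 31%, 21% or 18%; an excess of 10 points has 78%, 62% or 53%. This answers only whether unscheduled use in year 2 differs.
- *Cumulative use to month 24*, if the phrase were read that way. The visit within 3 months makes nearly everyone in both groups a yes, so the test is uninformative.

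**Step 4: cost time points.**

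| Place | Pre-operative | 12 months | 15, 18, 24 months |
|---|---|---|---|
| 8.3 | yes | yes | yes |
| Table 2 | no | no | yes |
| 10.3 (questionnaires) | – | – | yes |

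These cannot all be right.

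**The case against.** Several objections are sound and limit the point.

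- *COD has no anchor at all.* A reader might infer this, but the Summary, 8.3 and Table 2 anchor both groups at 1 year. The difficulty is that this anchor falls well after the strategies diverge.
- *The whole process endpoint is restricted to months 12–24.* The text attaches the phrase to the percentage only. Section 8.1.1 gives no window, and none is given for the mean or the Poisson model. The restriction of the count is therefore an inference, though 8.1.3 points the same way.
- *The endpoint is tautological or cannot be fitted.* This overreaches. A count is already planned and can show a net change. A large expected difference is not in itself a defect in a de-implementation trial, where disappearance of the routine visit is a legitimate outcome. Near-separation is not shown: at an assumed 95% attendance, 0.05 × 250 = 12.5, so some 12 or 13 RFU patients per joint would be a no.
- *The result changes direction.* Suppose RFU has 1 scheduled visit plus 0.1 and 0.2 unscheduled in the two intervals, and COD has 0.3 in each. The COD/RFU ratio is 0.6/1.3 = 0.46 over months 3–24, 0.3/1.2 = 0.25 over 12–24 with the scheduled visit, and 0.3/0.2 = 1.5 without it. The reversal needs a COD excess in year 2 and exclusion of the scheduled visit; equal year-2 rates give 1.0. With the visit counted, both windows favour COD.
- *Substitution in months 3–12 is established.* It is plausible, not evidenced. Both groups may contact a provider at any time (section 5).
- *The cost difference must carry the same error.* Costs also draw on electronic records (8.1.2, 8.3), so questionnaire timing alone does not fix the hospital-cost window.

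It can also be said that a counting rule belongs in the statistical analysis plan, which section 12.1 says will be published. That is fair for derivation detail. It does not cover placing months 3–12 outside the endpoints or the contradiction on cost time points, both of which the protocol itself fixes.

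**Conclusion.** The point holds in a limited form. As written, the protocol sets the process primary endpoint, at least for the yes/no percentage, to the year after month 12. On-demand visits and X-rays between the early visit and month 12 are then outside the primary comparison, although the primary objective concerns the whole strategies. With the scheduled visit counted, any shift of COD visits into that interval makes the net saving look too large, by a_C − a_R visits per patient. Under the assumed rates this runs from 0 to 0.6 (0.65 − 0.05).

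Separately, no rule says whether the scheduled 1-year visit and X-ray count. If they do, the yes/no test mainly reflects the schedule, given high attendance. If they do not, it omits the visit being removed and addresses only unscheduled use in year 2. The Poisson count is the better measure, but its window and counting rule are equally unstated.

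A reader might conclude that months 3–12 are lost. They are not: section 8.1.3 collects them. The fault lies in the endpoint definition. All rates and ratios here are illustrations, not estimates. The conflict over cost time points needs no assumption.

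**What to change.** In 8.1.1 and 10.1, define the process endpoint as the number of joint-related clinical visits, and separately X-rays, after the visit within 3 months up to 24 months after surgery, including the scheduled 1-year RFU visit and X-ray. Keep the count as the main process analysis and state that the Poisson model uses this window. Report unscheduled visits and X-rays separately over the same window, and use any unscheduled visit or X-ray as the yes/no measure. Amend 8.1.3 so that use after the early visit is no longer only an other parameter.

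For costs, reconcile 8.3 with Table 2 and 10.3, and state a cost window that covers hospital use in months 3 to 12 and the 1-year visit, taken from records where the questionnaires do not reach.

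For visits and X-rays the cost is wording only, since the record data are already planned. For costs, a 12-month questionnaire is extra work only if 8.3 is not already being followed. The change should be made before outcome data are examined.
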